### **11.2 Population to be analysed**

Data will be cleaned in the Statistical Package for the Social Sciences (SPSS) using procedures outlined in Tabachnick and Fidell (2007). Missing value analyses will be conducted and expectation maximisation techniques will be used to impute subscale data missing completely at random. Data will be imputed for participants completing at least 70% of items on that subscale; all other items on the subscale will be used to estimate missing data. If participants completed less than 70% of a subscale their data will be not imputed and the participant will not be included in analysis involving that subscale.

Both completer and intention-to-treat analyses will be conducted. Average closest match techniques (Elliot & Hawthorne, 2005) will be used to replace missing post and follow-up data for those who did not return questionnaires. This involves using the average post/follow-up-intervention value obtained by participants reporting the same pre-intervention score (or the four participants reporting the closest pre-intervention score), to replace the missing data for that case. This technique is considered a reliable and efficacious approach for managing missing data (Elliot & Hawthorne, 2005).

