#### Randomisation Procedures

Eligible parents will be randomised to either the parent intervention group or the W-L group. This will typically occur between three and four months post their child's diagnosis.

Three randomisation lists will be generated, one list per participating department. This will enable separate analysis by illness group as well as an overall exploration of outcomes for families of children with SCII. Each randomisation list will contain twenty six spaces. Participants will be randomly allocated to one of the two treatment arms using The RCH Department, Clinical Epidemiology and Biostatistics Unit (CEBU), computerised randomisation plan generator. This program will randomise each participant to one of the two treatment arms using the method of randomly permuted blocks. The end result will be two randomly allocated treatment arms of equal size divided between three randomisation lists organised according to Hospital Department (Cancer, Cardiac and PICU).

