## **7.5 Subject Withdrawal**

### **7.5.1 Reasons for withdrawal**

Participants are free to withdraw from the study at any time upon their request or the request of their legally acceptable representative.

The Research Team may withdraw a participant from the study (parent intervention and follow up procedures) if:

- During the course of the study, one of the exclusion criteria is met (e.g., the ill/injured child dies)
- The participant experiences a serious or intolerable adverse event
- Early discontinuation is required for any reason

The Researchers will also withdraw all participants from the study if the study is terminated.

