### **7.5.2 Handling of withdrawals and losses to follow-up**

When a participant withdraws from the study, the participant will be contacted by a RT member to discuss their reason/s for withdrawal if they have not already informed the research team. The interviewer will open conversation regarding withdrawal or non-participating by generally asking participants about their reasons for research discontinuation. Participants can choose not to take part in the call. Once a participant has withdrawn they are not required to complete any follow-up assessments and participation in the study is discontinued. Any information gathered during the course of the study from withdrawn participants will be kept unless participants request that their information be destroyed.

If RT members are concerned about the wellbeing (e.g., elevated scores on psychometric measures) of withdrawn participants actions to ensure the safety and wellbeing of these participants will be taken (e.g., referral information will be provided, families encouraged to link in with their nurse coordinator or social worker).

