## **11. STATISTICAL METHODS**

### **Sample Size Estimation**

In order to detect a difference of 6.0 (SD: 13.9) points (thought to be a clinically important difference in parents' experience of distress) in the Posttraumatic Stress Disorder Checklist (PCL- 5) measure, between the two treatment arms, with a significance level of 0.05 and power of 0.80, 82 participants will be required per arm. Allowing attrition, we therefore aim to recruit a total of 184

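### The intention-to-treat analysis replaces each unreturned post-program score with one fixed closest-match mean and then treats it as observed, so either the standard error or the treatment effect comes out too small

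*Protocol*

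**What the plan says.** Protocol section 11.2 plans a completer and an intention-to-treat analysis and names neither as primary. It sets two rules for missing data.

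- **Whole form not returned.** Average closest match is applied: "This involves using the average post/follow-up-intervention value obtained by participants reporting the same pre-intervention score". If there is no exact match, the mean of the four closest pre-scores is used. Each gap gets one value, with no random draw and no repeated imputation. The arm of the donors is not stated.
- **Form partly completed.** With at least 70% of a subscale's items answered, the remaining items are imputed by expectation maximisation. Below that: "If participants completed less than 70% of a subscale their data will be not imputed and the participant will not be included" in analyses of that subscale.

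Section 11.3 compares outcome means between arms with GEE models that allow for correlation within couples. Nothing there allows for imputation. (That section labels the comparison T3; the schedule in section 8.3 gives the post-program assessment as T4, which is used here.)

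Section 7.5.2 bears on how much data goes missing: "Once a participant has withdrawn they are not required to complete any follow-up assessments and participation in the study is discontinued".

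**The concern.** A donor mean carries less information than a real score. It has no residual scatter, and it reuses scores already in the data. If the analysis counts it as a full observation, the sample looks larger and less variable than it is.

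The donor arm decides what happens next. If donors come from the parent's own arm, the estimate is sound but the standard error is too small, so the test rejects too often. If donors come from both arms, the imputed scores carry almost no arm difference and the estimate is pulled towards zero.

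The two rules in section 11.2 also conflict. A parent who returns nothing is imputed and stays in the intention-to-treat set. A parent who answers 60% of the items is excluded, although more is known about that parent. On the 20-item PCL-5 the threshold is 0.70 × 20 = 14 items, so 12 answered items (60%) means exclusion.

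**Working it through.** **Inputs from the Protocol.** Sample Size Estimation gives the target difference ("In order to detect a difference of 6.0 (SD: 13.9) points") and, for the test and the size, "with a significance level of 0.05 and power of 0.80, 82 participants will be required per arm". The recruitment target after an allowance for loss is 184 in all. Randomisation Procedures: "two randomly allocated treatment arms of equal size", hence 184/2 = 92 per arm.

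**Assumptions, not in the Protocol.** Pre-post correlation 0.5 (0.3 to 0.7 also tried); scores missing completely at random; no couple clustering; loss of 20% and 30% as illustrations.

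**The plan's own figures.** With a two-sided test, n per arm = 2 × (1.960 + 0.842)² × 13.9² / 6.0² ≈ 84.2, so 85 rather than the stated 82. Power at 82 per arm is about 0.79. This small gap is a separate matter and does not affect the present point. No attrition rate is given; the implied one is 1 − (2 × 82)/184 = 20/184 = 10.9%.

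**Hand check, same-arm donors, 10.9% missing.**
- 82 real scores per arm support a standard error of 13.9 × √(2/82) = 2.17.
- Counting 92 scores as real gives 13.9 × √(2/92) = 2.05.
- A mean of four donors has variance of about 0.25 + 0.75/4 = 0.4375 of the full variance, so the filled-in sample has 0.891 + 0.109 × 0.4375 = 0.939 of it. The reported standard error falls to about 2.05 × √0.939 = 1.99.

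**Hand check, pooled donors.** Imputed scores contribute about zero arm difference, so the estimate is roughly 6.0 × (1 − share missing): 5.35, 4.80 and 4.20 at 10.9%, 20% and 30%.

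**Simulation.** 4,000 runs per cell, 92 per arm, SD 13.9, correlation 0.5. The section 11.2 rule was applied, followed by a Wald comparison of T4 means. Type I error is under no effect; the other columns are under a true difference of 6.0.

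| Missing | Same-arm: reported SE / true SE | Same-arm: type I error | Same-arm: 95% CI coverage | Pooled: estimate | Pooled: power | Observed scores only: power |
|---|---|---|---|---|---|---|
| 10.9% | 1.997 / 2.188 = 0.913 | 7.6% | 91.9% | 5.34 | 0.77 | 0.79 |
| 20% (assumed) | 1.959 / 2.306 = 0.850 | 9.5% | 90.1% | 4.78 | 0.68 | 0.74 |
| 30% (assumed) | 1.916 / 2.479 = 0.773 | 12.6% | 87.3% | 4.19 | 0.60 | 0.68 |

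The type I errors follow from the ratios. For example, a nominal 1.96 is really 1.96 × 0.913 = 1.79, with a two-sided tail of 7.4%. The Monte Carlo error of a 5% rate at 4,000 runs is √(0.05 × 0.95/4000) = 0.3 percentage points.

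**Sensitivity.**
- Across correlations of 0.3 to 0.7, same-arm type I error was 6.8-7.6% at 10.9% missing, 8.2-10.5% at 20% and 10.9-14.9% at 30%.
- With pooled donors it stayed near 5%.
- A separately programmed repeat gave 7.5%, 9.9% and 12.0% (same-arm), and 5.3, 4.8 and 4.2 points (pooled).
- Adjusting for the pre-score does not rescue the same-arm version: type I error was 8.5%, 11.0% and 15.8% (1,500 runs per cell).

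**Does the replacement work?** Multiple imputation by arm (20 imputations, Rubin's rules, pre-score as the only predictor, 1,500 runs per cell) gave type I error of 5.2%, 4.2% and 5.1%, coverage of about 95%, and estimates of 5.95 to 6.07 for a true 6.0.

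**The case against.** Several points on the other side stand.

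- **Donor arm.** The Protocol is silent rather than wrong on this. The cited methods paper or a separate SAP may settle it. But settling it only chooses between two faults: section 11.2 already fixes a single deterministic mean, and neither donor rule gives both a sound estimate and a sound standard error. A reader might infer that false positives are inflated in any case. They are not; with pooled donors the level holds.
- **Size.** Only about 10.9% loss can be read out of the documents, and the effect there is modest. The larger figures rest on loss rates that the Protocol does not give.
- **Completer analysis.** If it uses parents with observed T4 scores, this step does not touch it. In the simulated setting, observed scores alone gave type I error of about 5% and no bias. That limits the harm. It does not remove it, because the plan does not say which analysis carries the conclusion.
- **Part-completed forms.** A reader might infer that they are dropped in general. They are not: at 70% or more the items are imputed. Only subscales below 70% are excluded, and the documents give no frequency for these.
- **Withdrawal.** Section 7.5.1 lets the team withdraw a parent, for example when "During the course of the study, one of the exclusion criteria is met". TAB parents are monitored by their facilitator (section 8.2), so a reader might infer that such withdrawals fall mainly on the TAB arm. The Protocol gives no figure for this. Unequal random loss (about 16% TAB, 5% W-L, pooled donors) moved the estimate only from 5.34 to 5.27. Loss related to outcome was not simulated. Section 11.2 also does not say outright that withdrawn parents are imputed; that follows only if they count among those who did not return forms.

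The GEE model is not an answer. It deals with couples, and its standard error still takes imputed means as data.

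**Conclusion.** The point holds. As written, the intention-to-treat analysis does not give both a valid standard error and an unbiased effect under either donor rule. At the implied 10.9% loss the cost is one of two things: a standard error about 9% too small with type I error of about 7-8%, or a true 6.0 reported as about 5.3. At an assumed 20% and 30% loss the figures are about 10% and 12-13% type I error, or 4.8 and 4.2 points. All of this assumes random loss, a pre-post correlation of 0.5 and no couple clustering.

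The conflict between imputing an absent form and excluding one that is 60% complete needs no calculation. The effect of ending assessments at withdrawal is secondary and unquantified.

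The plan should be corrected, but this does not rank as a must-fix: the error is modest at the only loss rate that the documents imply, and the completer analysis is unaffected.

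**What to change.** - **Section 11.2, unreturned forms.** In the intention-to-treat analysis, replace average closest match with multiple imputation done separately by arm. Use T2 PCL-5, screening ASDS and department as predictors, allow for couples, and combine with Rubin's rules. Other methods that carry imputation uncertainty could also serve; the simplest form of this one was checked above.
- **Section 11.2, part-completed forms.** Treat a PCL-5 with under 70% of items answered as a missing total and impute it in the same way.
- **Section 11.2, role of the analyses.** Keep the completer analysis as a sensitivity analysis and say so.
- **Section 7.5.2 (secondary).** Separate stopping the program from leaving data collection. Keep inviting randomised parents to complete T4 unless they decline.

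The cost is Protocol and SAP wording, a little more programming, and one further questionnaire invitation for parents who stop the program. The change should be made before the data are analysed, since choosing a donor rule afterwards would mean choosing between two different answers.

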## 6. SUBJECT ENROLLMENT FOR SCREENING OF PARENTS

### 6.1 Recruitment

The details of the project and the study objectives will be provided to key staff from the RCH Departments via a face to face briefing. These staff will be asked to promote the study and the parent program to new families (within four weeks of diagnosis) attending the department for treatment. A screening process will be used to determine eligibility for the parent intervention program.

Participants will be parents of children during their first presentation for a diagnosis of cancer, cardiac disease, or who have been admitted to hospital in the PICU department. Participants will primarily be parents of children receiving inpatient services, however, in some instances parents may be seeking services for their child on an outpatient basis.

Participants will be asked to consent to participate in Screening in order to determine their eligibility into the RCT trial (parent intervention groups), to allow the research team to access their child's medical records for relevant medical and demographic information, and to consent to be recontacted in 3-6 months' time to be invited to participate in the RCT.

The Screening Questionnaire involves the completion of the ASDS on a single occasion within four weeks of their child's diagnosis (T1) along with the Demographic Questions. Parents who report pre-existing psychological conditions and/or other trauma/death will be considered ineligible for the RCT. The information obtained from the Screening Questionnaire, specifically the results from the ASDS, will provide key inclusion criteria regarding eligibility into the RCT. Parents **must score greater than or equal to 9 on items 1 to 5 (dissociation items) AND greater than or equal to 28 on items 6 through to 19 (combined items from hypervigilance, re-experiencing and avoidance subscales)** using the cluster scoring method. The ASDS will also provide important acute distress data on parents psychosocial functioning within four weeks of their child's diagnosis/surgery/admission and the demographic information gathered will ask about marital status, employment etc.

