### **331 SUBJECT ENROLLMENT AND RANDOMISATION FOR RCT**

#### **332 Recruitment**

333

334 Families determined as eligible from the Screening questionnaire (ASDS cluster scoring: a  
335 score of 9 or above on items 1 to 5 AND a score of 28 or above on items 6 to 19) will be  
336 invited to participate in the parent intervention program.

- 337 a. During the telephone call to invite parents to take part in the RCT the researcher  
338 will describe in full the requirements of participation in the efficacy trial. Parents  
339 will be sent a plain language statement and consent form (see Appendix 4: PICF  
340 – Parent Intervention Group – Parent Version) and a flyer detailing information  
341 about the TAB program. Parents will also be given the opportunity to ask  
342 questions. Parents will be asked if they would prefer the PICF to be sent via the  
343 mail or online. For those parents who have chosen to receive the PICF online,  
344 they will be provided with the option of having a copy of the PICF either mailed  
345 or emailed to them.
- 346 b. If neither parent is interested at that time, contact will cease unless the family  
347 indicates they would like time to consider the study.
- 348 c. If a parent is interested in participating they will be asked to sign and return the  
349 consent form to the Research Team in the provided reply paid envelope. For  
350 those parents who have selected to consent online, they can either return the  
351 signed PICF via email Parent and Researcher consent may therefore not be  
352 dated the same.
- 353 d. Upon receipt of signed consent forms, parents will be enrolled into the study  
354 and then randomly allocated to one of the two treatment arms.
- 355 e. If a family verbally consents to continue their participation when called, this  
356 verbal consent will be noted in the trial database. At this point, the parents will  
357 be enrolled into the study and then randomly allocated to one of the two  
358 treatment arms. The researcher will again encourage the participating parent to

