return written or online consent. If a parent requires the consent form to be mailed out again, or if an email consent form is preferred, then the form will be sent to the family once more, in another attempt to obtain written consent. If we again have difficulty obtaining formal written or online consent, a second verbal consent will be obtained over the phone prior to questionnaires being sent out and participation in the program commences. During this same phone call, a member of the research team will determine days and times that best suit the parent for attending a parent program and schedule them into a group. Parents allocated to the W-L arm will be advised when to expect the first set of questionnaires and advised of the approximate starting month for their participation in a group (following the completion of their post questionnaire).

- f. Pre-assessment measures will be distributed two weeks prior to the commencement of TAB group sessions to parents enrolled in the two treatment arms. Pre-assessment measures must be completed by parents prior to the commencement of the parent program. Parents have the choice to complete the questionnaires online or via paper/pen format.
- g. Any pre-assessment measures not returned/completed prior to the commencement of the parent program will be followed up. Parents allocated to the W-L arm will be followed up individually via their preferred method of contact. For those parents within the W-L arm that have failed to return written consent forms, another consent form will be sent with these pre-questionnaires, and they will be encouraged to return the signed consent forms when they return the pre-assessment measures.

Parents may choose to withdraw permission to participate at any time and request removal of their information from the database.

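### The intention-to-treat rule for a missing T4 needs a T2 score collected after randomisation, so it cannot score a randomised parent who returns neither

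*Protocol*

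**What the plan says.** Section 11.2 plans both completer and intention-to-treat analyses. For parents who do not return post or follow-up questionnaires, the missing score is replaced by the average "value obtained by participants reporting the same pre-intervention score" or, failing an exact match, by that of the four parents nearest on the same score. The section's other imputation rule works on items: a subscale is completed only if at least 70% of its items were answered, and otherwise the parent is left out of analyses of that subscale.

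The order of events is set out under enrolment and randomisation for the RCT. "Upon receipt of signed consent forms, parents will be enrolled into the study" "and then randomly allocated to one of the two treatment arms" (Recruitment, item d; item e does the same for verbal consent). Randomisation Procedures gives the timing: "This will typically occur between three and four months post" diagnosis. Under section 7.4 the parent is then contacted about the allocation. Only after that does item f apply: "Pre-assessment measures will be distributed two weeks prior to the commencement of TAB group sessions to parents enrolled in the two treatment arms". Section 8.3 labels this assessment T2 (Pre), and Table 2 places it at week 20. Item f requires T2 before the program starts, and item g adds: "Any pre-assessment measures not returned/completed prior to the commencement of the parent program will be followed up".

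The measure taken before randomisation is the screening questionnaire, which section 6.1 describes as "completion of the ASDS on a single occasion within four weeks" of diagnosis, together with demographic questions.

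**The concern.** An intention-to-treat analysis is meant to compare the arms as randomised. Here the matching variable is not a pre-randomisation measurement. Parents can be lost between allocation and T2, and by then they know whether they are offered a group now or, under section 7.4, in two to six months. Loss in that interval can depend on the arm. A parent lost there has no T2 to match on and no T4 to analyse.

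This is a different problem from single imputation understating the variance. In this case the rule produces no value at all. If those parents leave the analysis, the comparison loses some of the protection that randomisation gives, in the one analysis intended to keep it.

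**Working it through.** **1. Order of events.** Consent, then randomisation, then disclosure of arm, then T2, then sessions, then T4. Randomisation at three to four months is about weeks 13 to 17. With T2 at week 20, the gap is 20 - 17 = 3 to 20 - 13 = 7 weeks if Table 2 counts from diagnosis, and longer if it counts from screening. Section 8.2 adds waiting time: a group starts only when at least five TAB parents are available, and wait-list questionnaires are timed to that group.

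**2. What the stated rules give for each pattern of return.**

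| T2 | T4 | Result under section 11.2 |
|---|---|---|
| yes | yes | observed |
| yes | no | closest match on T2 |
| no | yes | observed; section 11.3 states no baseline covariate, so T2 is not needed |
| no | no | no match possible; fewer than 70% of items answered, so not imputed |

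Only the last row is at issue.

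**3. The plan's own figures.** Sample Size Estimation (section 11) gives a difference of 6.0, SD 13.9, alpha 0.05, power 0.80, 82 per arm and 184 in total.
- Two-sided normal formula: n = 2 x (13.9 x (1.960 + 0.842) / 6.0)^2 = 84.25, so 85 per arm. The stated 82 is not reproduced exactly, but its power is 0.789, close to 0.80. The present point does not rest on this.
- 82 / 0.90 = 91.1, so 92 per arm and 184 in total.
- Planned attrition: 184 - 2 x 82 = 20, and 20/184 = 10.9%. This covers losses of every kind; the protocol does not split them into before and after T2.

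**4. Size of a possible bias.** Let f be the share of an arm with neither T2 nor T4, and d the mean T4 difference between those parents and the rest of that arm. Leaving them out shifts the TAB minus wait-list estimate by f(WL) x d(WL) - f(TAB) x d(TAB). No value of f or d is in the protocol, so these are assumptions:
- Loss in one arm only, f = 5-10%, d = 4-7 points (about 0.3-0.5 SD): 0.05 x 4 = 0.2 to 0.10 x 7 = 0.7 points. Against the target: 0.2/6.0 = 3% to 0.7/6.0 = 12%.
- Equal f and equal d in both arms: 0.
- Simulation with 92 per arm, no true effect, a correlation of 0.6 between early distress and outcome, and more distressed parents more likely to be lost: about 0 with 10% lost in each arm; about -1.0 point (favouring TAB) with 15% lost in TAB and 5% in wait-list; about -1.3 with 20% and 5%.

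For scale, the standard error of the difference with 82 per arm is 13.9 x sqrt(2/82) = 2.17 points, so 0.2-0.7 points is about 0.1-0.3 of a standard error.

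**5. Power.** With all 184 parents in the analysis, power for 6.0 points is 0.833. If 5%, 10% or 20% cannot be scored, it is 0.814, 0.793 or 0.745.

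**The case against.** The strongest reply is that section 11.2 only leaves a sub-case unsaid, and that handling of a missing baseline commonly belongs in a statistical analysis plan, which may exist. That is right about the wording: a reader might infer that the protocol excludes these parents outright, and it nowhere says so. But the protocol does more than stay silent. It fixes the matching variable for an analysis it calls intention-to-treat, and that rule, followed as written, cannot score every randomised parent. A later plan that kept to it would inherit the gap.

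Second, item f requires T2 before the program and item g has non-returns followed up. Both narrow the path. Neither closes it, because no analysis rule covers a T2 that never arrives, and section 7.5.2 asks for no assessments after withdrawal.

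Third, it is tempting to add that every parent who consents verbally receives T2 only after a second consent. The text does not support that: the second verbal consent applies only where written or online consent is still outstanding after a further attempt.

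Fourth, the effect may be small and is unquantified. This stands. The bias figures are assumed, amount to a fraction of a standard error, and vanish if loss is alike in both arms.

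Fifth, the ASDS may not be held for everyone randomised. Parents may have their data removed, and the inclusion criteria let a partner take part alongside the eligible parent. That is fair, so the proposed set excludes data withdrawn on request, and a missing ASDS can itself be imputed.

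**Conclusion.** The point holds as a gap in a stated rule. By implication, the intention-to-treat analysis omits randomised parents with neither T2 nor T4, and they can be lost after learning their arm. A parent with T4 but no T2 is not affected.

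The number on this path is unknown. A reader might take 20 of 184 as its upper limit, but that is the planned allowance for all attrition and bounds nothing here. The 0.2-0.7 point shift rests on assumed loss confined to one arm and an assumed outcome difference; the protocol gives no evidence that loss will be unequal. The point justifies a change to the analysis text. It does not show that the trial's result would be materially biased.

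**What to change.** In section 11.2:
- Define the intention-to-treat set as all randomised parents whose data have not been withdrawn at their request.
- Replace the closest match on T2 alone with multiple imputation by arm, using the T1 ASDS scores and department, plus T2 PCL-5 when available.
- Analyse each imputed data set with the GEE of section 11.3, so that within-couple correlation is kept.
- Report the number per arm with neither T2 nor T4.

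The cost is revised wording and some programming. No new data are needed, because the ASDS is taken at screening and the randomisation lists are by department. The downside is that the ASDS, taken months before T4, is a weaker predictor than T2 PCL-5. For parents without T2, the imputation lessens bias from arm-related loss only as far as ASDS and department explain it, so the shifts shown above are not the amount the change would remove.
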